### Participants

Eligible participants will be postgraduate residents pursuing a less than 6-year residency in pediatrics, pediatric emergency medicine fellows, and registered nurses from the pediatric ED (aged >18 years). Written informed consent will be obtained from each participant in the experimental group after full information disclosure prior to study participation. On the first day, after completing the informed consent form, participants will be asked to download the app to their personal smartphone through the secure institutional Microsoft Intune portal (Microsoft Corporation). They will then be required to attend a unique standardized 5-minute introduction course to the app and its functionality by the study investigators, but they will not receive specific instructions on how often to use the app. The participants will remain the same throughout the intervention period. No one will be asked to advise on the interpretation of the results.

### Setting

The study will take place in the pediatric ED of a tertiary referral and major trauma hospital in Switzerland, with an annual volume of 35,000 visits. This should represent approximately 16,600 visits over the 6-month prospective intervention period, of which approximately one-half could potentially benefit from laboratory tests. The ED has 14 centrally monitored treatment rooms, a resuscitation room, a 5-bed short-term observation room (ie, <24 hours), a plaster room, a hypostimulation room, and a dedicated interview room. The patient population consists of local children from birth to 16 years of age with medical, surgical, and traumatology emergencies, as well as transfer cases from other hospitals in Switzerland or children located in neighboring France.

The usual number of residents is 10 on a monthly basis during a 4-month period. They provide coverage for 6-7 overlapping shifts, which begin at different times, with each shift ranging from 10 hours (9 hours of patient care, 1 hour of recovery) to 12 hours (12 hours of patient care, no recovery time at night) on weekdays and 6 shifts on weekends to cover a 24-hour day (Table 1). During the intervention schedule, residents typically work 3-4 night shifts followed by 72 hours off, then 3-5 consecutive day shifts before 2 days off, followed by 2-day shifts. This pattern repeats throughout the month, with occasional additional days off or vacations. The 14 fellows (some of whom are part-time) work in an irregular combination of 6 overlapping 8-12 hour shifts on weekdays and 3 shifts on weekends (Table 1). Finally, 17 nurses out of a total of 43 cover a 24-hour day. This represents a total coverage of 70-78 hours, 30-48 hours, and 102 hours per day for residents, fellows, and nurses, respectively. The ED uses the Canadian Triage Acuity Scale [21] to guide patient treatment based on medical-surgical urgency. On average, each resident sees about 300 patients per month and fellows 50-70, with a ratio of medicine: surgery-trauma cases of 2/3:1/3. The standard physician-to-patient ratio ranges from 1:5 to 1:7 and varies according to disease acuity and time of the visit. The nurse-to-patient ratio ranges from 1:3 to 1:5. Caregivers see patients on a first-view [22], on-site, 24/7 basis. Whether they work 8-, 10-, or 12-hour shifts, they all work in the same area, have access to the same patient volume, and see the same patient complaints. They have full, secure 24/7 electronic access to laboratory results.

**Table 1 table1:** Work shifts by time of day and occupation.

Caregiver and work shift		Count, n	
		Weekdays	Weekend
**Residents**			
	7:45-17:45	1	0
	8:00-20:00	1	2
	10:00-22:00	1	1
	14:00-24:00	1	0
	16:00-2:00	1	1
	20:00-8:00	1	1
	21:00-9:00	1	1
**Fellows**			
	7:30-16:30	1	0
	8:00-18:00	1	0
	8:00-20:00	0	1
	14:00-20:00	1	0
	14:30-23:00	1	0
	15:30-24:00	1	0
	20:00-8:00	1	1
**Nurses**			
	7:00-15:30	5	5
	11:30-20:00	1	1
	15:00-23:30	6	6
	23:00-7:15	5	5

### The PIMPmyHospital Mobile App

Information regarding the app has been published previously [16]. In brief, the app was developed iteratively following a user-centered approach starting with the identification of the main functionalities that meet end-user needs [15]. The system operates on a client-server architecture. Four microservices developed on the Java Spring Boot framework ensure (1) transmission of patient information, (2) access to real-time laboratory results, (3) the trigger of push notifications, and (4) exchange of information between caregivers through an instant messaging system. These microservices exchange information with the front end developed in the Angular and Ionic frameworks through a restful app programming interface. Patient medical data are not stored on the app itself, but in the institution’s EMR on secure servers to which the app connects. The exchange of data between the app and these servers is secured by the use of JSON web tokens obtained during the authentication of caregivers through a Keycloak identity and access management solution. User authentication on the device relies both on a login password and a specific certificate installed on the user’s device. The app runs on Google’s Android and Apple’s iOS operating systems.

The app’s interface features a home page with a personalized view of the patients that each caregiver is taking care of, together with associated information (eg, patient identity, time since admission, and patient’s geospatial location within the ED) and clickable actions next to them [16]. In particular, dropdown contextual tabs provide real-time access to laboratory results retrieved from the hospital patient’s EMR. Visual push notifications occur as soon as new results are made available. The entire patient management process is available to the caregiver in the palm of their hand and can be accessed at any time while on the go, hence the app’s name “Patients in my Pocket.”

### Procedure and Intervention

This is a pre-post study. Before the implementation of the app, EMR-based data from the past 12 months will be collected retrospectively. These data will include the times (ie, HH:MM:SS) that results issued by the central laboratory were available on the institutional EMR as well as the times at which these results were accessed by caregivers through conventional computerized workstations. After the implementation of the app, data will be collected prospectively over a 6-month period of use. This will include the times (HH:MM:SS) when the results issued by the central laboratory are made available through the app on caregivers’ smartphones and access times as well as concurrent or preferred access times on the conventional computerized workstations should this occur. Individual acceptance of the app on the first day (a priori) and then on the last day of the intervention will be evaluated through the Unified Theory of Acceptance and Use of Technology (UTAUT) [23]. Usability of the app will be measured by the System Usability Scale (SUS) [24]. Figure 1 shows the study procedure, and Table 2 presents the study schedule. Use of the app will be on a 24-hour basis and at the discretion of participants.

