### Outcomes and Measures

#### Primary Outcome: Time to Laboratory Access

The primary outcome will be the mean elapsed time in minutes between the delivery of the laboratory results and the caregiver accessing them, both before and after the implementation of the app.

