### Data Collection

Electronic data will be extracted from the institutional data lake. The data lake stores all data and events from the EMR information system in a database and can be retrieved using Simple Protocol and RDF Query Language (SPARQL) queries. In the preintervention period, the time stamp of the laboratory results on the EMR will be identified as the time of issuance of the said results. Access to these results by the physicians and nurses will be defined by the time stamp of the first access to the laboratory results’ viewer on the EMR. Access to results on the app will be computed either by the time stamp of the push notification access or to the dedicated page on the app. No other patient-level data such as identifiers or clinical characteristics will be collected. Collected data will be transmitted to the REDCap database web app (REDCap, Vanderbilt University) hosted by the hospital for analysis.

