### Statistical Analysis

The association of app use with the time between delivery of the laboratory results and their access by caregivers will be assessed using generalized estimating equations with an exchangeable correlation structure to account for the nested structure of the outcome (ie, time) within the physicians. To account for potential differences in case-mix and physician characteristics, we will use multivariable generalized estimating equations. The covariates will be as follows: (1) the triage acuity scale, (2) type of pathology (medical, surgical-traumatological, psychiatric), (3) experience of the caregiver expressed in years since certification, (4) patient age, (5) patient sex, (6) workload represented by the number of patients present in the emergency room, (7) time of day or night, (8) day of the week, and (9) month of the year (seasonal variability). To account for the possible effect of exogenous factors that would impose an asymmetry in the data (skewness on the right) by extending the awareness of laboratory results, we will identify these factors as the study progresses prospectively and take them into account in the final analysis. The same analyses will be performed for the nurses. We will carefully monitor and evaluate through descriptive analyses any differences between nurses’ and physicians’ frequency access to laboratory results. If the target sample size cannot be reached, we will first extend the prospective data collection period by 3 months (deemed ethically acceptable as not impacting patients) or present only the results of qualitative user experience interviews.

For the technology acceptance self-administered survey questionnaire, scores on the 8 technology acceptance constructs will be described using descriptive statistics. Items on the SUS questionnaire will be described using frequencies. Analyses will be carried out using R software (R Core Team) [27]. All statistical tests will be 2-sided, with an α risk of .05.

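### None of the nine covariates for the primary outcome describes the laboratory result, so a change in test mix between the two periods could be read as an app effect

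*Protocol article*

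**What the plan says.** The primary outcome (Protocol article, Primary Outcome: Time to Laboratory Access) is the "mean elapsed time in minutes between the delivery of the laboratory results and the caregiver accessing them", before and after the app. It is neither restricted nor stratified by kind of test.

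Procedure and Intervention describes the retrospective data: "These data will include the times (ie, HH:MM:SS) that results issued by the central laboratory were available on the institutional EMR", plus the times at which caregivers opened them. Results are therefore those of the central laboratory, with no distinction among them.

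Data Collection defines access on the electronic record as "the time stamp of the first access to the laboratory results" viewer, and adds: "No other patient-level data such as identifiers or clinical characteristics will be collected".

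Statistical Analysis sets out a multivariable generalized estimating equations (GEE) model to deal with differences in case-mix and in the physicians. The list opens: "The covariates will be as follows: (1) the triage acuity scale, (2) type of pathology (medical, surgical-traumatological, psychiatric". It continues: "3) experience of the caregiver expressed in years since certification, (4) patient age, (5) patient sex". The remaining four are workload, time of day or night, day of the week and month of the year. The section also promises to find, during the prospective phase, outside factors that lengthen the times and skew them to the right, and to allow for them in the final analysis.

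**The concern.** Exposure is defined by calendar period. Study Design calls this a nonequivalent comparison, 12 months before against 6 months after. Anything that differs between the periods and affects access time enters the app effect unless a covariate carries it.

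The thing being timed is a laboratory result, yet the covariate list has no term for it. It is plausible, though not documented, that a result awaited for an immediate decision is opened sooner than one that is not. Two medical patients at the same triage level can have quite different tests, so triage and a three-level pathology code are partial proxies. Month of the year handles patterns that recur each year, but not a change from one year to the next. The plan itself expects right-skewed times, and a mean of such times is sensitive to a small class of slowly opened results. The distortion could go either way: it could mimic a benefit of the app or hide one.

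**Working it through.** **Step 1: the covariate list.** Each item in Statistical Analysis, by what it describes:
- patient: triage, pathology type, age, sex
- caregiver: years since certification
- department: number of patients present
- calendar: time of day, weekday, month

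That is 4 + 1 + 1 + 3 = 9 items, of which 0 describe the result.

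**Step 2: the plan's own scale.** Inputs from Sample Size and Statistical Analysis: effect 0.5 SD, power 90%, two-sided 5%, intraclass correlation 0.1, and 100 patients per month over 3 months, so 300 per physician.
- Two-sample calculation: 85 per group, 170 in total.
- Design effect: 1 + (300 − 1) × 0.1 = 30.9.
- Patients: 170 × 30.9 = 5253, the stated figure.
- Physicians: 5253 / 300 = 17.5, so 18, as stated.

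The sample size is not in dispute. It gives the planned precision: SE = √(4 × 30.9 / 5253) = 0.153 SD.

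**Step 3: size of the possible bias.** With two classes of test, bias = (change in share of one class that the covariates do not absorb) × (difference in mean access time between the classes). The documents give neither input; both are assumed below. The last column is the two-sided type I error at SE 0.153 SD when the app has no effect.

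| Share change | Class gap | Bias | As % of 0.5 SD | Type I error |
|---|---|---|---|---|
| 5 points | 0.5 SD | 0.025 SD | 5% | 5.3% |
| 10 points | 0.5 SD | 0.05 SD | 10% | 6.2% |
| 20 points | 0.5 SD | 0.10 SD | 20% | 10.0% |
| 5 points | 1 SD | 0.05 SD | 10% | 6.2% |
| 10 points | 1 SD | 0.10 SD | 20% | 10.0% |
| 20 points | 1 SD | 0.20 SD | 40% | 25.6% |

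**Step 4: the same in minutes, as an illustration only.** Assume 20 min for fast tests, 220 min for slow tests, and a slow share of 10% before and 7% after.
- Before: 0.90 × 20 + 0.10 × 220 = 40 min.
- After: 0.93 × 20 + 0.07 × 220 = 34 min.
- Fall: 6 min, or 6/40 = 15%, with no app effect.
- SD between classes before the app: 200 × √(0.10 × 0.90) = 60 min, so the fall is 6/60 = 0.1 SD. Spread within classes would make it smaller still.

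A drop that looks sizeable as a percentage is thus about one fifth of the target effect and less than one SE.

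**Step 5: two sections side by side.** Data Collection rules out further patient-level data, naming clinical characteristics. Statistical Analysis needs triage, pathology, age and sex. Both cannot stand. If the first does, four of the nine covariates are lost, including the partial proxies for test type.

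**The case against.** The strongest reply is that the bias is conjecture. No section reports that access times differ by test, or that the test mix changed between the years. November to April falls in both periods, so month adjustment covers seasonal mix, and triage, pathology and age carry some of the rest. This stands: the concern is conditional and its size is unknown.

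A second reply is that the promise to account for outside factors already covers it. That helps little. The factors are unnamed and are to be identified in the prospective phase, so nothing secures a test field for the retrospective year.

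A third concerns the unit. Sample Size counts patients, and access is the first opening of the viewer, so one observation may cover several tests and a single test-category variable may be undefined. This stands, and the fix must allow for it. It also means the article does not show that every single result is a separate observation.

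A fourth is that test type may itself be affected by the app, since later orders can depend on results seen earlier. This stands as a caveat: adjustment removes only the difference in mix between the chosen categories, and may remove a small part of an app effect.

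A reader might also infer that nothing but time stamps will be extracted. The documents do not support that. Procedure and Intervention says what the data will include, which is not exhaustive; Data Collection bars other patient-level data, which need not exclude a test category; and the planned look at alerts for pathological values would need an attribute of the result.

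**Conclusion.** The point holds in a limited form. The primary comparison is one mean over central-laboratory results in two non-randomised periods, and the enumerated list intended to handle case-mix has no term for the result. A change in test mix that does not recur seasonally, and that triage, pathology type and age miss, would be attributed to the app.

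Under the assumed inputs the bias is 5% to 40% of the target effect. The low end is negligible; the high end would raise the type I error from 5% to about 26%. The plan as written gives no means of telling which applies.

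It would go too far to say that the mean will move, or by how much: that needs both a difference in access time between test classes and an unabsorbed shift in mix, and neither is documented. This is an inexpensive strengthening of a stated covariate list, not a flaw that invalidates the design.

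**What to change.** 1. In the data-lake query already planned, extract the laboratory's test category with each release time, in both the retrospective and the prospective period.
2. Add it to the multivariable GEE for physicians and for nurses. If one viewer opening covers several tests, enter indicators for the categories contained in the release.
3. Report the test mix by period, so that readers can see whether it changed.
4. Show the app estimate with and without the term, and note that ordering after implementation may be slightly influenced by the app.
5. Reconcile Data Collection with Statistical Analysis, stating whether triage, pathology type, age and sex are collected.

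The cost is one non-identifying field and a few degrees of freedom in a model planned for thousands of observations. No new patients or procedures are needed, and the term may also reduce residual variance.

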### Objectives

In this study, we present the protocol for a pre- and posttest study. Its objective is to evaluate whether the use of the *PIMPmyHospital* app alters ED physicians’ and nurses’ temporal efficiency to access laboratory results more quickly while actively working in an ED. Temporal efficiency will be assessed by measuring the time between the release of the laboratory results in the clinical information system and their acknowledgment by these clinicians. To our knowledge, no app that can access laboratory results in real time in the ED has been described to date [17]. The study will be structured according to the “Population,” “Intervention,” “Comparison,” and “Outcome” framework as follows: (1) participants: medical and nursing staff working in the pediatric ED; (2) intervention: implementation of the mobile app in the pediatric ED; (3) comparison: remote access to laboratory results in the pediatric ED through the app versus standard access to laboratory results prior to its implementation; (4) outcomes: times to access laboratory results, ED-LOS, technology acceptance, and app’s usability among users, and how specific in-app alerts impact on its effectiveness.

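### The primary outcome's start and stop time stamps are not aligned between the pre-app and post-app periods, so part of the contrast may be a change of instrument of unknown size and direction

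*Protocol article*

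**What the plan says.** **General definitions.** The Objectives section describes one interval: "the time between the release of the laboratory results in the clinical information system and their acknowledgment by these clinicians". The primary outcome section also uses one wording for both periods, the "mean elapsed time in minutes between the delivery of the laboratory results and the caregiver accessing them, both before and after" implementation, but does not tie delivery to a particular system.

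**Before the app.** Data Collection sets the start: "In the preintervention period, the time stamp of the laboratory results on the EMR will be identified as the time of issuance". Procedure and Intervention agrees, recording when "results issued by the central laboratory were available on the institutional EMR". The stop is "defined by the time stamp of the first access to the laboratory results" viewer on the EMR.

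**After the app.** Procedure and Intervention lists the times "when the results issued by the central laboratory are made available through the app" on smartphones, the app access times, and any workstation access times. Data Collection computes app access "either by the time stamp of the push notification access or to the dedicated page on the app".

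**Route of access.** The Methods paragraph of the Abstract pairs EMR access with the period before and app access with the period after. Procedure and Intervention, by contrast, also records workstation access after implementation and leaves app use to the participants' discretion.

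**The concern.** The study has one primary contrast, before against after. If the interval is measured by different events on the two sides, the change of instrument falls exactly on that contrast. None of the nine covariates in the Statistical Analysis section (acuity, pathology, experience, age, sex, workload, time of day, weekday, month) can separate it from the effect of the app.

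Three things are left open or in tension for the post period: which stamp starts the clock, which app event stops it, and whether a workstation access can stop it. Each choice changes the estimated difference in minutes without any change in how quickly caregivers see results.

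**Working it through.** **1. The possible clocks.** For one result, let R be EMR release, A availability on the app, N notification access, P opening of the app results page, and V opening of the EMR viewer after release.

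- Pre period: V − R.
- Post period, matching clock: min(V, P) − R.
- Post period, app start stamp: min(V, P) − A, which is the matching clock minus (A − R). The app section says that results are retrieved from the EMR, so A ≥ R and this can only shorten the time. If V comes before A, the recorded time is negative.
- Post period, notification stop: min(V, N) − R. Where N precedes P, this is never longer than the matching clock, and it is shorter whenever N also precedes V.
- Post period, app access only: P − R. Where V comes before P, this exceeds the matching clock by P − V. Results seen only at a workstation have no app time and drop out, with unclear direction.

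The first two departures favour the app. The last can go against it. The article does not say which combination applies, so the net sign is not determined.

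**2. The plan's own sample size, as a base for scale.** Inputs from the Sample Size section: effect 0.5 SD, power 90%, 5% level (two-sided per Statistical Analysis), intraclass correlation 0.1, and 100 patients per month over 3 months, so 300 per physician.

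- Per period without clustering: 2 × (1.960 + 1.282)² / 0.5² = 84.06, rounded up to 85.
- Design effect: 1 + (300 − 1) × 0.1 = 30.9.
- Total: 2 × 85 × 30.9 = 5253, the stated figure. 5253 / 300 = 17.5, so 18 physicians.

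The stated figure reproduces, and the point here does not rest on it.

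**3. What a pure clock shift would do.** Assume no true effect and a shift of s SD in one direction. Effective size per period is (5253 / 2) / 30.9 = 85, so the standard error is √(2/85) = 0.153 SD. The two-sided rejection probability is Φ(s/0.153 − 1.96) + Φ(−s/0.153 − 1.96).

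| Assumed shift (SD) | Rejection probability (nominal 5%) |
|---|---|
| 0.02 | 5.2% |
| 0.05 | 6.2% |
| 0.1 | 10.0% |
| 0.2 | 25.6% |
| 0.3 | 49.8% |

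A shift of a few hundredths of an SD is negligible, while 0.2 SD is serious. With no lag, tap-to-view gap or SD in minutes in the documents, the shift cannot be placed in this table.

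**The case against.** The strongest reply is that the outcome is defined once for both periods, in the Objectives and in the primary outcome section, and that Procedure and Intervention only lists data to be collected. It does not declare app availability to be time zero. That stands: a post-period start on the phone is not fixed by the article. But the rule tying the start to the EMR stamp is expressly limited to the period before the app, and nothing extends it.

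The app section also describes real-time retrieval from the EMR and notifications sent as soon as results are available, so the lag may be trivial. This stands too, though no figure is given. The dedicated app page is close in kind to opening the EMR viewer, and accessing a notification may itself open the result. The article does not say whether it does. Opening the EMR viewer is also only a proxy for reading the values.

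A reader might infer that the clocks are known to differ in the app's favour, by a minute or more. The documents do not support this. They give no lag, and an app-only counting rule would push the other way.

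Finally, an article commonly leaves time-stamp derivation to the full protocol or analysis plan. That would answer mere silence. Here the article does state measurement rules, and states them differently for the two periods.

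**Conclusion.** The point holds as a misalignment in the definition of the primary outcome, not as a demonstrated bias. The start rule is stated for one period only and is in tension with the Objectives. The app stop event can be something other than display of the result, and the Abstract and the Procedure section differ on whether post-period workstation access counts.

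The net size and direction cannot be determined from the documents. The rejection probabilities above assume no true effect, a pure one-directional shift and the plan's own design effect. They show that the issue could be negligible or serious. It should be settled before analysis because it bears on the only primary comparison.

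**What to change.** Reconcile the Abstract, Objectives, Procedure and Intervention, Primary Outcome and Data Collection sections to one clock for both periods:

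- **Start:** the EMR release time stamp.
- **End:** the first opening, after release, of a page displaying the result (EMR viewer or app results page), whichever comes first.

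Report the EMR-to-app lag descriptively. Use notification access as the endpoint only in a sensitivity analysis.

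The cost is small. Table 2 already schedules EMR-based data in the posttest period, and Data Collection already names access to the app page, so the time stamps should be obtainable. The sample size stays at 5253. The downside is that the estimated benefit may be slightly smaller.
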